### Primary safety study parameter

Incidence of bleeding complications according to E-CABG classification, grade 1 and higher [31]. For the bleeding complications, a non-inferiority test will be used. We test the hypothesis that the difference in bleeding between the intervention group and the control group is below the a priori specified boundary of 11%. This will be tested using a one-sided *t* test with an alpha of 0.025, with the null hypothesis that the number of bleedings is above the threshold margin and the alternative hypothesis that is below the threshold margin. If the confidence interval for the bleeding complications does not include the non-inferiority limit in the per-protocol analysis and in the intention-to-treat analysis, non-inferiority for bleeding complications is established.

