### Sample size calculation {14}

In the DSAA (2014 to 2016), the rate of serious complications was 29% for all patients. According to the Society for Vascular Surgery AAA 2018 guidelines, the incidence of TEC is between 15 and 36%. In our preliminary MANCO trial, the incidence of TEC was 14%. For our power calculation, the incidence of TEC is set at 14%. The vast majority of mortality after open AAA repair stems from TEC. A mortality rate of 5% after open AAA repair is derived from DSAA. The hypothesis is that a decrease of TEC will result in a lower mortality of 3%. Bleeding complications derived from the literature and from our MANCO trial and ACTION pilot study are 18–39% (scored according to E-CABG classification) [30].

Derived from data from our pilot study and from literature, the hypothesis is that ACT-guided heparinization will lower the rate of TEC to 8%. The expected incidence for the combined endpoint of TEC and mortality is therefore set at 19% for the 5000 IU group and 11% for the ACT-guided group. Using a continuity corrected chi-square test with a two-sided alpha of 5%, 337 patients are needed in each group to achieve a power of 80%. Including a dropout of 10%, a total of 750 patients are needed for the combined primary endpoints of TEC and mortality.

In our pilot study, no increase in bleeding complications was found for open AAA repair (E-CABG class 1 bleeding was 39% versus 36%). Nevertheless, it is important that excessive bleeding does not occur in the intervention group. Therefore, a non-inferiority calculation was performed. Bleeding complications and TEC are different and have a different impact on patients. Bleeding complications grade 1 E-CABG have less impact on mortality and quality of life than TEC. The expectation is an improvement in combined TEC and mortality of 8%, and the non-inferiority for bleeding complications is set at 11%.

Expecting 32% bleeding complications in the standard group and 33% in the intervention group and a non-inferiority limit of 43% (11% limit difference) with a power of 80% and a one-sided alpha of 5%, 272 patients are required in each group. Therefore, the 750 patients which are needed for the combined primary endpoints of TEC and mortality are sufficient to also evaluate the non-inferiority for bleeding complications.

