### Main study parameter/endpoint safety {12}

Incidence of bleeding complications according to E-CABG classification, grade 1 and higher: per- or postoperative transfusion of 2 or more units of red blood cells, transfusion of platelets, transfusion of fresh frozen plasma, or re-operation for bleeding during the hospital stay [30, 31]. For the bleeding complications, a non-inferiority test will be used. This will be tested using a one-sided *t* test with an alpha of 0.025.

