### Other study parameters {12}

#### Preoperative parameters

Patient demographics: sex, smoking history, body length and weight and body mass index, medical history (general, cardiac, pulmonary, diabetes, surgical), medication, all previous vascular interventions; blood pressure and pulse at the outpatient visit, ECG reports; diameter and anatomical classification of abdominal or iliac aneurysms; preoperative laboratory results: Hb, leucocytes, sodium, potassium, creatinine, eGFR, platelets; presence of impaired renal function (eGFR < 40 ml/min).

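### The bleeding non-inferiority test is valid but unadjusted, and gives up some precision that preoperative haemoglobin, already collected, could supply

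*Protocol article*

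**What the plan says.** The safety endpoint is E-CABG grade 1 or higher. Under Main study parameter/endpoint safety, a patient counts through "per- or postoperative transfusion of 2 or more units of red blood cells, transfusion of platelets, transfusion of fresh frozen plasma" or through re-operation for bleeding.

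Primary safety study parameter fixes the analysis, with a margin of 11 points: "We test the hypothesis that the difference in bleeding between the intervention group and the control group is below the a priori specified boundary of" that size. The method is a one-sided t "test with an alpha of 0.025, with the null hypothesis that the number of bleedings is above the threshold margin". The claim must hold "in the per-protocol analysis and in the intention-to-treat analysis, non-inferiority for bleeding complications is established". No covariate is named there, in the endpoint section or in the general Statistical analysis section.

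Preoperative parameters lists "preoperative laboratory results: Hb, leucocytes, sodium, potassium, creatinine, eGFR, platelets". Randomisation is stratified by centre only.

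Sample size calculation gives the assumptions: "Expecting 32% bleeding complications in the standard group and 33% in the intervention group and a non-inferiority limit of 43% (11% limit difference"), and, "with a power of 80% and a one-sided alpha of 5%, 272 patients are required in each group".

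**The concern.** Whether a patient receives two units of red cells plausibly depends on the Hb before surgery as well as on blood lost. An endpoint defined mostly by transfusion therefore probably has a baseline predictor, and it is already on the case report form. A test that ignores it leaves the variance Hb explains in the error term.

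At stake is the second half of the trial's claim: fewer thrombo-embolic complications and deaths without more major bleeding. Non-inferiority is tested confirmatorily only after efficacy succeeds, and it must then hold in two analysis sets. The protocol names a specific unadjusted test for a primary endpoint, so this is a choice it has made rather than a detail left to an analysis plan.

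**Working it through.** **Inputs.** From Sample size calculation: control rate 0.32, intervention rate 0.33, margin 0.11, 337 evaluable per arm, 750 in total (375 per arm), sizing alpha one-sided 0.05. From Primary safety study parameter: analysis alpha one-sided 0.025. The share of outcome variance explained by baseline Hb (R²) is not in the article and is assumed.

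**Step 1: reproduce the plan's figure.** The distance from the expected difference to the margin is 0.11 − (0.33 − 0.32) = 0.10. The variance term is 0.32×0.68 + 0.33×0.67 = 0.2176 + 0.2211 = 0.4387.

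n per arm = (z₁₋α + z₀.₈₀)² × 0.4387 / 0.10²

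- One-sided 0.05: (1.645 + 0.842)² × 43.87 = 271.2, so 272. This matches the article.
- One-sided 0.025: (1.960 + 0.842)² × 43.87 = 344.3, so 345. This exceeds the 337 evaluable patients per arm.

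**Step 2: unadjusted power.** SE = √(0.4387/n); power = Φ(0.10/SE − z₁₋α).

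| n per arm | SE | alpha 0.025 | alpha 0.05 |
|---|---|---|---|
| 337 | 0.0361 | 79.2% | 87.0% |
| 375 | 0.0342 | 83.2% | 90.0% |

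For comparison, efficacy (19% versus 11%) has 80% power at 337 per arm with the continuity correction and 83.0% with the plain chi-square test. Non-inferiority is thus the weaker comparison at alpha 0.025, but not at 0.05.

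**Step 3: power with adjustment.** A covariate explaining R² of the outcome variance shrinks the standard error by √(1 − R²): power = Φ(0.10/(SE·√(1 − R²)) − 1.960). At 337 per arm and alpha 0.025:

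| Assumed R² | Power | Gain (points) |
|---|---|---|
| 0 | 79.2% | – |
| 1% | 79.6% | 0.4 |
| 5% | 81.2% | 2.0 |
| 10% | 83.2% | 4.0 |
| 15% | 85.2% | 6.1 |

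Gains are taken before rounding. Power reaches 80% when R² = 1 − 337/344.3, about 2.1%. As a guide to scale, with a 32.5% event rate and normally distributed Hb, odds ratios per SD of Hb of 1.25, 1.5, 2.0 and 2.5 correspond to R² of about 1%, 3%, 9% and 14%.

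**Step 4: the per-protocol set.** The article does not give its size. At assumed sizes of 300, 270 and 240 per arm, unadjusted power at alpha 0.025 is 74.4%, 69.9% and 64.8%. With R² = 10% and 270 per arm it rises from 69.9% to 74.4%.

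**Step 5: effect of chance imbalance.** A one-standard-error imbalance in mean Hb moves the risk difference by about ρ × SE. For an assumed correlation ρ of 0.2 to 0.4, that is 0.7 to 1.4 points, against a standard error of 3.6 points that already includes this variation.

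**The case against.** The strongest reply is that nothing here is an error. An unadjusted comparison of randomised arms is valid, and choosing a simple test over a more efficient one is partly preference. That stands, and it limits the point to efficiency.

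Four stronger readings are tempting, and the article does not support them.

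- **Unequal starting Hb could cause a false pass or fail.** Chance imbalance is already covered by the unadjusted test's standard error and error rate. Adjustment narrows the interval; it does not repair an invalid test.
- **Red-cell transfusion drives the endpoint.** The definition shows that three of four components are transfusions. No component frequencies are given, so which one dominates is unknown.
- **The gain is large.** A correlation of 0.5 (R² 25%) would add about 10 points at 337 per arm, but needs an odds ratio of about 4 per SD of Hb. Nothing in the article supports that. For odds ratios of 1.25 to 2.0 the gain is roughly 0.4 to 3.5 points.
- **Power is tightest on this endpoint.** This is true only at alpha 0.025. At the 5% used for sizing, power is 87.0% to 90.0%, above efficacy. The apparent shortage comes from the conflict between the two stated alphas, which is a separate and larger matter that adjustment does not resolve.

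It can also be said that adjusted analyses are usually left to an analysis plan. That carries less weight here, because the protocol itself fixes the unadjusted test as the one that decides non-inferiority.

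**Conclusion.** The point holds as a modest, inexpensive gain in precision that the plan leaves unused. At the stated analysis alpha and 337 per arm, unadjusted power is 79.2%. Adjustment for Hb would add about 0.4 to 6 points if R² lies between 1% and 15%. The range rests on an assumed Hb–outcome association, on the plan's bleeding rates and on a normal approximation. If the association is very weak, almost nothing is gained and little is lost. Because the claim must also hold in the smaller per-protocol set, some extra precision is worth having. This ranks below reconciling the alpha of 5% in the sample size section with the 0.025 in the analysis sections.

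**What to change.** Before unblinding, amend Main study parameter/endpoint safety and Primary safety study parameter as follows:

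- Estimate a standardised (marginal) risk difference from a logistic model with arm, continuous preoperative Hb and centre, the stratification factor, with small centres pooled by a stated rule. Allow no optional covariates.
- Give a robust or bootstrap 95% confidence interval and compare its upper limit with the same 11-point margin. The estimate remains a marginal risk difference, so the margin keeps its meaning.
- Apply this in both the intention-to-treat and per-protocol sets.
- Keep the unadjusted difference as a sensitivity analysis.
- State that missing baseline Hb is singly imputed without regard to arm. Otherwise the rule in Statistical analysis that excludes subjects with missing data from each analysis would drop those patients.

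The cost is protocol wording and slightly more analysis code. No new data are needed. The code may fall outside the standard menus of SPSS, which the article names for all analyses, so that sentence may need a small allowance.

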### Secondary study parameter(s)

Secondary endpoints include all complications as defined by DSAA and suggested standards for reports on aneurysmal disease. Health status was measured with the EQ-5D-5L questionnaire. Differences in categorical outcomes between the intervention and control groups will be expressed as the absolute risk difference with a 95% confidence interval. Differences in continuous outcomes will be tested with Student’s *t*-test in case of a normal distribution or the Mann-Whitney *U*-test in case the data do not follow the normal distribution. The level of significance is set at a two-sided *P*-value < 0.05.

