### Secondary study parameters/endpoints {12}

Secondary endpoints: complications (non-TEC), within 30 days postoperative or in the same admission, as defined by DSAA and suggested standards for reports on aneurysmal disease: all complications requiring re-operation, longer hospital stay, and all other complications; incidence of kidney injury as defined by RIFLE criteria: rise of serum creatinine > 100% or decrease of eGFR with 50% [35]; allergic reactions; ACT values (in the intervention group), total heparin administration, and protamine administration; peroperative blood loss, blood transfusions either autologous or homologous, other blood product administration, total operative time, aortic clamping time, use of adjunctive hemostatic products, and length of hospital (including ICU) stay; health status as measured with the EQ-5D-5L; and economic and health care cost evaluation by IMCQ and IPCQ and addition of out-of-pocket expenses.

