### Recruitment {15}

Patients scheduled to undergo open AAA repair will be informed about the study by their attending vascular surgeon in the outpatient clinic of participating hospitals about the study and the informed consent procedure will be explained. Informed consent will only be obtained by medical personnel who are GCP licensed. Also, a mandatory training by research staff has to be completed and the site initiation visit (SIV) completed {26a}. This SIV is performed by an external, independent trial research organization: Julius Clinical. A total of 750 patients with an abdominal aortic aneurysm requiring open aneurysm repair will be included in the ACTION-1 study, after signing informed consent (Fig. 1). An EQ-5D-5L questionnaire is handed out to the patient after receiving informed consent. The patient returns the form by post to the investigators, or bring the form when admitted for surgery, for baseline values. Figure 2 shows the participant timeline {13} and Fig. 3 shows the study schedule.

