### Statistical analysis {20 a,b,c}

Descriptive statistics of continuous variables will be presented as means with standard deviations (SD) or medians with inter-quartile ranges (IQR) depending on the distribution of the data.

Categorical data will be presented as proportions and numbers. The statistical efficacy analysis will be conducted according to the intention-to-treat principle. A separate per-protocol analysis will be performed additionally as a sensitivity analysis. All analyses will be performed with the latest version of the Statistical Package for Social Sciences (SPSS, SPSS Inc., Armonk, NY, USA).

The analysis of primary efficacy and safety outcomes will be performed on an intention-to-treat basis and in a hierarchical fashion. If the statistical analysis shows that there is a statistically significant difference in the primary efficacy endpoint, a statistical analysis of the primary safety study parameter will be performed. If there is no significant difference between study groups in primary efficacy endpoint, assessment of primary safety endpoint will be considered exploratory. Subjects with missing data will be excluded per analysis.

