### Other study parameters

Peroperative blood loss (continue), blood transfusions either autologous or homologous (categorical), other blood product administration (categorical), total operative time (continue), clamping time (continue), use of adjunctive hemostatic products (categorical), length of hospital (including ICU) stay (continue), and health status (categorical and continue); ACT values measured (continue); the amount of heparin and protamine used (categorical). The outcomes of the first 5 patients from all participating hospitals will be analyzed and compared with the outcomes of patients included later. Data on the previous heparin protocol will be collected per hospital. Analyses will be conducted to determine whether the previously used heparin protocol affects the outcomes.

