## Economic evaluation

### Cost-effectiveness analysis (CEA)

General considerations: We hypothesize that ACT-guided heparinization could lower the rate of TEC and TEC-related mortality to in total 11% and that the quality of life can be increased from 73 to 76%. The economic evaluation of ACT-guided heparinization against standard care with a standardized bolus of heparin will be performed as cost-utility analyses and a cost-effectiveness analysis from a societal perspective with the costs per quality-adjusted life year (QALY) and the costs per prevented complication as the primary economic outcomes. The cost-utility analysis can be used for policy making and composition of a guideline. The cost-effectiveness analysis (CEA) relates to the clinical outcome parameter and may be used for prioritization or benchmarking of strategies that enhance surgical patient safety. The CEA and CUA will be based on a time horizon of 6 months. All related complications are within the time horizon of 6 months and patients will be recovered from the surgery. For on-going complications such as leg amputations, colostomy, permanent neurological deficits, and dialysis, a CEA and CUA with a lifelong time horizon will be made using extrapolation and model-based techniques. For this time horizon, discounting of effects and costs will be performed as stated in the most recent guidelines for cost analysis [36]. To account for uncertainties in the lifelong time horizon, a probabilistic sensitivity analysis will be performed.

Incremental cost-effectiveness ratios will be calculated as the difference in costs per QALY gained and as the difference in costs prevented complications. Sampling variability will be accounted for by bias-corrected and accelerated non-parametric bootstrapping. Results will be reported along with their 95% confidence intervals and displayed graphically with cost-effectiveness planes and with cost-effectiveness acceptability curves. One-way and multi-way sensitivity analyses will be done for the unit costs of the most common complications. Some missing data can be expected; if missing data is at random, this will be handled through multiple imputations with predictive mean matching.

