### Patient outcome analysis

Patients will be asked to complete the EQ-5D-5L health status questionnaire at baseline, 1 week, 4 weeks, 13weeks, and 26 weeks after surgery. These forms can be completed online or at home by the patients and send to the investigators by post. These questionnaires will be included in the CRFs. The EQ-5D-5L scoring profiles can be converted into a health utility score based on general population-based Dutch tariffs [37]. QALYs will be calculated for each patient using linear interpolation between the successive health utility assessments over time.

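### EQ-5D-5L is measured before surgery, yet the stated secondary comparison is an unadjusted t or Mann-Whitney test, which is valid but gives up precision

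*Protocol article*

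**What the plan says.** All references are to the protocol article.

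- Secondary study parameters/endpoints {12} lists "health status as measured with the EQ-5D-5L" among the secondary endpoints. Other study parameters, in the statistical part, classes health status as both categorical and continuous.
- Recruitment {15}: "An EQ-5D-5L questionnaire is handed out to the patient after receiving informed consent". The form is posted back or brought to the admission for surgery, and its stated purpose is to supply baseline values.
- The section Patient outcome analysis gives the schedule: "Patients will be asked to complete the EQ-5D-5L health status questionnaire at baseline, 1 week, 4 weeks, 13weeks, and 26 weeks after surgery".
- Secondary study parameter(s) names the EQ-5D-5L and then sets the test: "Differences in continuous outcomes will be tested with" Student's t, or Mann-Whitney if the data are not normal, at a two-sided 0.05 level. No covariate is named.
- Statistical analysis {20 a,b,c}: "Subjects with missing data will be excluded per analysis".
- Cost-effectiveness analysis (CEA) hypothesises that "the quality of life can be increased from 73 to 76" percent. That section has its own missing-data rule for the economic evaluation: multiple imputation with predictive mean matching if data are missing at random.

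**The concern.** A patient's health status before surgery usually predicts health status afterwards. Here it is collected from every willing patient and then left out of the comparison between arms. A two-sample test at a single visit leaves in the noise all the between-patient variation that the baseline could explain. It also lets any chance baseline difference between arms pass into the estimate. Four postoperative assessments are planned, but a t or Mann-Whitney test uses them one at a time. Under the exclusion rule, a patient without a form at a given visit contributes nothing to that visit's comparison.

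What is at stake is the precision of a patient-reported secondary endpoint for which the article hypothesises only a small difference. The primary endpoint and the sample size are not affected.

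**Working it through.** **Step 1. The plan's own figure.** The article gives a sample size only for the primary composite. Inputs from Sample size calculation {14}: 19% vs 11%, two-sided alpha 0.05, power 80%, continuity-corrected chi-square.

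- Uncorrected: n = [1.96·√(2·0.15·0.85) + 0.8416·√(0.19·0.81 + 0.11·0.89)]² / 0.08² = (0.9897 + 0.4223)² / 0.0064 ≈ 311.6, so 312 per group.
- Corrected: n′ = (311.6/4)·[1 + √(1 + 4/(311.6·0.08))]² ≈ 336.1, so 337 per group.
- With 10% dropout: 337/0.9 = 374.4, so 375 per group and 750 in total.

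The stated 337 and 750 reproduce and are not in dispute. The article states no power, SD or sample size for EQ-5D-5L.

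**Step 2. Inputs for EQ-5D-5L.**

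- Difference: 3 points, from the hypothesised 73 to 76 (read as 0.03 on the utility scale).
- Patients per arm: 337, the evaluable number behind the sample size.
- SD: assumed 15, 20 or 25. The article gives none.
- Correlation r between the baseline and the follow-up score: assumed 0.3, 0.5 or 0.7. The article gives none.

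**Step 3. Effect of adjustment.** ANCOVA on baseline multiplies the residual variance by 1 − r²: 0.91, 0.75 and 0.51 at r = 0.3, 0.5 and 0.7. For equal precision that corresponds to 9%, 25% and 49% fewer patients.

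Power = Φ( 3 / [SD·√(1 − r²)·√(2/337)] − 1.96 ).

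Worked case, SD 20:

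- √(2/337) = 0.0770, so the unadjusted standard error is 1.541.
- r = 0: 3/1.541 = 1.947, and Φ(1.947 − 1.96) = 0.495.
- r = 0.5: 1.947/0.866 = 2.248, and Φ(2.248 − 1.96) = 0.613.

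| Assumed SD | Unadjusted | r = 0.3 | r = 0.5 | r = 0.7 |
|---|---|---|---|---|
| 15 | 74% | 78% | 85% | 95% |
| 20 | 50% | 53% | 61% | 78% |
| 25 | 34% | 37% | 44% | 59% |

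With 375 per arm and SD 20 the row becomes 54%, 58%, 66% and 82%. These figures are for one visit compared by a t test or ANCOVA. They do not include any further gain from modelling the four visits jointly.

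**The case against.** The strongest reply is that nothing here is wrong. Randomisation makes the unadjusted comparison unbiased, and EQ-5D-5L is an unpowered secondary endpoint. The sentence on tests is generic: it also serves blood loss, operating time and length of stay. The 3-point gain is an economic hypothesis, not the target of this test, and SD and r are assumed. All of this stands, and it limits the point to precision. It does not remove the point, because the article names the test for a section that names the EQ-5D-5L. An analysis plan that followed this text would leave the baseline unused.

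Three stronger readings are tempting, and the article does not support them.

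- *The cost-per-QALY analysis drops patients with missing data.* The exclusion rule stands in the clinical analysis section. The economic evaluation has its own multiple-imputation rule.
- *Deaths are treated as missing in the QALYs.* No text says so: QALYs are to be calculated for each patient. A condensed article may leave the value given to death, and any baseline adjustment of QALYs, to the full plan.
- *Half of the hypothesised gain is ignored because deaths drop out.* The planned mortality of 5% vs 3%, times a score of about 75, gives 0.02 × 75 = 1.5 points, half of 3. That comparison assumes that 73 to 76 describes survivors, which the article does not say. If the figures already count death as 0, survivors would score 73/0.95 = 76.8 and 76/0.97 = 78.4, and the 1.5 points would already be part of the 3. All-cause mortality is also part of the primary composite, so it is tested in its own right.

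**Conclusion.** The point holds as a loss of precision. The article collects a baseline EQ-5D-5L and fixes a comparison that does not use it. The direction is certain for any non-zero baseline correlation. The size depends on assumptions: at SD 20, power for 3 points goes from about 50% to between 53% and 78%. Over SD 15 to 25 the unadjusted power alone runs from 74% down to 34%.

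The unadjusted test is not biased, the sample size is untouched, and the point does not reach the missing-data handling of the economic evaluation. It is a worthwhile improvement to a secondary analysis, not a threat to the trial's main conclusion.

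One limit applies to the remedy. A mixed model uses all returned forms, but it does not itself account for patients who die, so the result has to be labelled for what it is.

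**What to change.** In Secondary study parameter(s), take EQ-5D-5L out of the generic test sentence and state that:

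- it will be analysed by ANCOVA at a named visit, or by a repeated-measures mixed model with baseline EQ-5D-5L, centre, arm, visit and arm-by-visit as terms, using all available visits;
- the effect is the adjusted mean difference with a 95% confidence interval;
- it is a comparison among patients alive, reported beside mortality;
- patients without a baseline form are kept by a stated rule, since otherwise the per-analysis exclusion would drop them from an adjusted model.

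The visits must also be reconciled first: Follow-up and quality of life measurements gives 1, 4, 16 and 23 weeks, while Patient outcome analysis gives 1, 4, 13 and 26.

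As an optional and consistent step, include baseline utility as a covariate when the QALY difference is estimated within the bootstrap.

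The cost is wording only. The data are already collected, and no extra patients, visits or forms are needed. The change should be made before unblinded outcome data are analysed.
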